# Effectiveness of the addition of therapeutic alliance with minimal intervention in the treatment of patients with chronic, nonspecific low back pain and low risk of involvement of psychosocial factors: a study protocol for a randomized controlled trial (TalkBack trial)

**DOI:** 10.1186/s13063-017-1784-z

**Published:** 2017-01-31

**Keywords:** Low back pain, Empathy, Subgroups, Minimal intervention

## Abstract

**Background:**

The stratified model of care has been an effective approach for the treatment of low back pain. However, the treatment of patients with low risk of psychosocial-factor involvement is unclear. The addition of the therapeutic alliance to a minimal intervention may be an option for the treatment of low back pain. This paper reports on the rationale, design and protocol for a randomized controlled trial with blind assessor to assess the effectiveness of the addition of therapeutic alliance with minimal intervention on pain and disability in patients with chronic, nonspecific low back pain.

**Methods:**

Two hundred and twenty-two patients with chronic, nonspecific low back pain and low risk of involvement of psychosocial factors will be assessed and randomly allocated into three groups (*n* = 74 patients per group). The Positive Therapeutic Alliance group will receive counseling and guidance with an emphasis on therapeutic alliance and empathy. The Usual Treatment group will receive the same information and counseling with limited interaction with the therapist. The Control group will not receive any intervention. The treatment will be composed by two intervention sessions with a 1-week interval. A blinded assessor will collect the following outcomes at baseline, 1 month, 6 months and 12 months after randomization: pain intensity (Pain Numerical Rating Scale), specific disability (Patient-specific Functional Scale), general disability (Oswestry Disability Index), global perceived effect (Global Perceived Effect Scale), empathy (Consultation and Relational Empathy Measure), credibility and expectations related to treatment. The analysis will be performed using linear mixed models.

**Discussion:**

This will be the first study to understand the effect of combining enhanced therapeutic alliance to a treatment based on counseling, information and advice (minimal intervention). The addition of the therapeutic alliance to minimal intervention may improve the treatment of chronic, nonspecific low back pain.

**Trial registration:**

ClinicalTrials.gov, NCT 02497625. Registered on 10 July 2015.

**Electronic supplementary material:**

The online version of this article (doi:10.1186/s13063-017-1784-z) contains supplementary material, which is available to authorized users.

## Background

Low back pain remains a global public health problem [1]. It is considered to be the sixth leading cause of disability-adjusted life years among more than 200 health conditions [1, 2]. Despite the increase in quantity and quality of research in recent decades, the available treatments for low back pain tend to produce minor or moderate effects. These effects are positive in the short term and only some of them maintain long-term improvements [3]. The high prevalence of low back pain makes impossible the use of treatment strategies that demand high resources for all patients [4]. Studies have shown that a small group of patients who develop chronic pain are responsible for most of the treatment-related costs [5, 6]. Thus, it is important to identify patients who would benefit from a specific treatment from those who would show little benefit or even worsening of symptoms [4].

Low back pain is an ideal condition for the stratification of treatment subgroups since it is a condition that affects a heterogeneous population, presenting prognostic variation and relying on different diagnostic options and available treatments [4, 7, 8]. Stratification based on the prognosis of the clinical condition is a form of classifying low-back-pain patients in subgroups and it is based on the risk of developing persistent pain and disability related to psychosocial factors [4]. Psychosocial factors (e.g., depression, stress, aspects related to work and fear of movement [9]) are predictive for the occurrence of new episodes and the long-term persistence of pain and disability [8, 10–12]. Treatment in subgroups may also facilitate the clinical decision-making process and guide appropriate treatment for these patients [4]. Moreover, it may assist therapeutic decision-making, maximize treatment benefits, reduce risks and increase health system efficiency [8, 13].

Recent studies have shown the cost-effectiveness of the treatment based on the chronic low back pain prognosis in patients with high and medium risks of developing chronic problems related to psychosocial factors [8, 14]. Positive results were associated with decreased pain and disability, in addition to reduction in cost and work absenteeism [7, 14]. However, the results of a recent randomized controlled trial showed no significant differences for patients with low-risk of involvement of psychosocial factors when compared the usual treatment and targeted treatment based on subgroups [15]. These negative results may be explained by the fact that patients already presented low levels of pain and disability and by the use of questionnaires with low responsiveness for low-risk patients [16]. Disability questionnaires frequently used to evaluate patients with low back pain are not sensible to detect a clinical change in patients with low level of disability. For this kind of patients, it is recommended to use specific questionnaires of disability [16]. In the treatment of these low-risk patients it is recommended that information and guidance be provided on correct diagnosis, prognosis, symptoms, physical activity levels, return to work and disease severity, preferably at the first contact with the health professional [9, 17, 18]. Considering the good prognosis of low-risk patients, some studies suggest a minimal intervention approach (counseling sessions and positive information) [7, 17]. This approach might be a quick and low-cost treatment option to the health system. Furthermore, identifying appropriate treatment for each patient may prevent the unnecessary use of expensive or extended resources [4]. There is also the possibility of reducing the use of diagnostic procedures (imaging tests, for example), decreasing the number of consultations during the recovery process and consequently less use of financial resources. Thus, some studies emphasize the need to develop more effective treatment strategies for this patient subgroup [7, 8, 14]. One of the possibilities of the nonsignificant results deriving from minimal intervention with these patients is that patients with low risk of developing chronic problems have low to medium levels of pain and disability. Therefore, it is necessary to evaluate patients using measurement instruments that are more responsive to this clinical condition [16].

The extent of treatment effectiveness may be influenced by factors other than the intervention chosen. Contextual factors comprise the therapeutic effect of any intervention. These factors consist of a complex interaction between technical and communicative knowledge in addition to the therapist’s ability to meet the expectations of the patient during treatment [19]. Studies have shown that a good relationship between the therapist and patient is related to decreased pain level and disability as well as improved satisfaction with treatment [20, 21]. The therapeutic alliance may be defined as harmony or social connection between therapist and patient [22]. However, both the magnitude and extent of this association in musculoskeletal patients are unknown [21]. This gap in the medical literature reinforces the need for studies on this subject, especially in the treatment of patients with musculoskeletal complaints. Emerging evidence indicates that the degree and quality of the interaction between clinician and patient is important because it influences the magnitude of the active treatment, as well as the degree of placebo effect [21, 23, 24]. Although therapeutic alliance has been shown to produce therapeutic benefits in some areas, such as medicine and psychotherapy, there is little empirical support yet for this subject in physiotherapy [20, 21]. A recent systematic review showed a consistent pattern of positive therapeutic alliance correlated with improved pain, disability and treatment satisfaction in physical rehabilitation [21].

A recent study investigated the effects of increased therapeutic alliance and empathy in the treatment of patients with low back pain receiving active interferential current or a placebo. Patients were randomly allocated into four groups: (1) limited interaction plus active current, (2) limited interaction plus placebo, (3) increased interaction plus active current and (4) increased interaction plus placebo. The results showed clinical improvement associated with increased interaction between therapist and patient, which remained even with the application of placebo [25]. This study evaluated the effects only in the short term and did not classify patients into specific treatment subgroups. Therefore, the rationale of this study is based on emerging evidence of the importance of the therapeutic alliance in the clinical context [19, 21, 23–29].

Appropriate treatment for low-risk patients can provide important clinical benefits. It could be a fast and low-cost treatment option for the health system since it would help in identifying patients who do not require unnecessary or extensive assessment and treatment [4]. To date, there are no studies that have investigated the therapeutic alliance combined with minimal intervention in the treatment of patients with chronic, nonspecific low back pain and low risk of psychosocial-factor involvement. Therefore, the objective of this study is to evaluate the effectiveness of the addition of the therapeutic alliance with minimal intervention in the treatment of patients with chronic, nonspecific low back pain with a low risk of having psychosocial-factor involvement in their pain, specific and general disability, global perceived effect, empathy, credibility and expectation. The hypothesis of this study is that there will be a clinical benefit in pain, and especially in specific disability, 1 month after randomization into the group receiving treatment with the addition of the therapeutic alliance.

## Methods

### Study design

This is a three-arm randomized controlled trial with blinded assessor. The patients will be divided into three groups: a Positive Therapeutic Alliance (PTA) group, a Usual Treatment (UT) group and a Control group (CG). Table 1 details the study timeline and follows the style of the Standard Protocol Items: Recommendations for Interventional Trial (SPIRIT) guideline. The SPIRIT Checklist and figure for the study protocol are provided as Additional file 1 and Additional file 2. The World Health Organization Trial Registration Data Set is provided as Additional file 3.

**Table 1 Tab1:** Timeline for the schedule of enrollment, interventions and assessments

Results	Recruitment	Before randomization	Post baseline (after first session)	Intervention period	Reassessment 1 month after randomization	Reassessment 6 months after randomization	Reassessment 12 months after randomization
Eligibility criteria	X						
Demographic data	X						
Informed consent	X						
Primary outcomes							
Pain intensity		X			X		
Specific disability		X			X		
Secondary outcomes							
Pain intensity						X	X
Specific disability						X	X
General disability		X			X	X	X
Global perceived effect		X			X	X	X
Additional outcomes							
Empathy			X				
Credibility			X				
Expectation			X				
Interventions							
Increased therapeutic alliance				X			
Usual treatment				X			
Control group				X			

### Sample size calculation

The sample size calculation was carried out to detect a difference of 1 point on the Pain Numerical Rating Scale (estimated standard deviation = 1.84) and 1 point on the Patient-specific Functional Scale (estimated standard deviation = 1.8). The calculations were performed considering an *α* = 0.05, a statistical power of 80% and a follow-up loss of 15%. Thus, this study will comprise a sample of 222 patients who will be divided into three treatment groups (*n* = 74 patients per group).

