### Statistical analysis

A researcher not involved in data collection and without any conflict of interest will be responsible for monitoring data. The randomization process and blinding of patients and assessors will be audited monthly by an experienced researcher. All data will be entered twice before statistical procedures. A researcher who will receive the data in an encrypted format to ensure confidentiality will conduct the statistical analysis.

Linear mixed models will be used for primary analysis to verify the differences between the average effects of interventions in reassessments carried out 1 month, 6 months and 12 months after randomization. The differences between groups will be calculated by interaction terms of groups versus time. The time will be coded as a categorical variable (baseline, 1 month, 6 months and 12 months after randomization). No interim analysis will be performed. The process of analysis of treatment efficacy will follow the intention-to-treat analysis [44]. If a patient abandons treatment or refuses to answer any reassessment, the lost data will not be replaced. All statistical procedures will be performed with a significance level of 5% and through the SPSS 19 software for Windows.

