## Discussion

The results of this study will help us to understand the effect of combining increased therapeutic alliance with a type of treatment based on advice, information and advice for patients with chronic low back pain and low risk of psychosocial-factor involvement. We believe that the UT group will present significantly better treatment results when compared to the CG. Regarding the PTA group, the study hypothesis is that: 1 month after randomization, there will be a significant clinical decrease in pain and especially in specific disability, when compared to the other two study groups. This assumption is based on recent studies, which have shown that the therapeutic alliance does in fact have a positive influence on clinical outcomes of patients with irritable bowel syndrome [23], rehabilitation needs [21] and chronic musculoskeletal disorders [29]. Treatment adherence appears to be directly influenced by patients’ trust and empathy with the health care professional. Thus, decreased specific disability may occur because the patient follows the guidelines provided by the health care professional with more confidence. Our research group expects to publish the results of this study in an internationally recognized journal and to release the spreadsheet with the data encoded during the first semester of 2018.

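### The 74 patients per arm do not follow from the stated inputs: a two-group comparison gives 65 (pain) or 62 (PSFS), and 74 per arm gives about 86–87% power, not 80%

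*Protocol article*

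**What the plan says.** The Sample size calculation section of the protocol article sets the target for pain as "a difference of 1 point on the Pain Numerical Rating Scale (estimated standard deviation = 1.84"). The second target, for specific disability, is "1 point on the Patient-specific Functional Scale (estimated standard deviation = 1.8"). On error rates it says "The calculations were performed considering an *α* = 0.05", with "a statistical power of 80% and a follow-up loss of 15" per cent. It then draws its conclusion: "Thus, this study will comprise a sample of 222 patients who will be divided into three treatment groups", with 74 in each.

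The section does not name the test, its sidedness, or which pair of groups the difference refers to.

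The Statistical analysis section plans linear mixed models with time as a categorical variable: "The differences between groups will be calculated by interaction terms of groups versus time". It also says: "All statistical procedures will be performed with a significance level of 5" per cent. It describes neither a split of alpha nor an omnibus comparison of the three arms.

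The Assessments section makes pain and specific disability at 1 month the primary outcomes. The Discussion expects the Positive Therapeutic Alliance (PTA) group to do better on both "when compared to the other two study groups". It separately expects Usual Treatment (UT) to do better than Control.

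**The concern.** The paragraph gives the usual ingredients of a two-group calculation and presents 222 as their result. A reader who repeats the calculation gets a clearly smaller number: 9 fewer per arm for pain, or 27 fewer in total. That is more than rounding.

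Two explanations are possible, and they have opposite implications for power. If the test is an ordinary pairwise comparison at 5%, the trial is larger than it needs to be and 80% understates its power. If alpha was divided or a global test was used, 80% holds for PSFS at best and is slightly too high for pain, the outcome with the larger SD. The printed text fits neither reading, so a reader cannot tell what power a null PTA-versus-UT result should be judged against.

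**Working it through.** **Inputs** (all from the Sample size calculation section): difference 1 point; SD 1.84 (pain) and 1.8 (PSFS); alpha 0.05; power 80%; loss 15%; three equal arms of 74. Two-sided testing is an assumption, because the text does not give the sidedness.

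**1. Attempt to reproduce 74 from the stated inputs.** Normal approximation, n per arm = 2 × (z₁₋α/₂ + z₁₋β)² × SD² / difference²:

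- Pain: 2 × (1.960 + 0.842)² × 1.84² = 53.1, so 54.
- PSFS: 2 × (1.960 + 0.842)² × 1.8² = 50.9, so 51.

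With the t distribution (noncentral t) these become 55 and 52. Allowing for loss:

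| Outcome | Evaluable per arm (t) | ÷ 0.85 | × 1.15 |
|---|---|---|---|
| Pain | 55 | 64.7, so 65 | 63.25, so 64 |
| PSFS | 52 | 61.2, so 62 | 59.8, so 60 |

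The larger requirement is 65 per arm, or 3 × 65 = 195 in total. The normal approximation gives 54 / 0.85 = 63.5, so 64 per arm and 192 in total. One-sided testing moves further away: 43 evaluable and 51 randomised for pain. None of these gives 74.

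**2. Power that 74 per arm provides.** 74 × 0.85 = 62.9, about 63 evaluable per arm. For one pairwise t-test at two-sided 0.05:

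- Pain: 86% (0.857).
- PSFS: 87% (0.872).

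**3. What would bring the number close to 74.**

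- *Alpha 0.025, two-sided.* With SD 1.8 the t-test needs 63, and 63 / 0.85 = 74.1. With SD 1.84 it needs 66, and 66 / 0.85 = 77.6, so 78. The normal approximation for SD 1.84 gives 64.4, and 64.4 × 1.15 = 74.0.
- *Three-group F test at 0.05, means 0, 0.5 and 1.* With SD 1.8 it needs 64, and 64 × 1.15 = 73.6, so 74 (64 / 0.85 = 75.3, so 76). With SD 1.84 it needs 67, which is 78 or 79 per arm.

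Power of these two alternatives with 63 evaluable per arm:

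| Test | Pain (SD 1.84) | PSFS (SD 1.8) |
|---|---|---|
| Pairwise, alpha 0.025 | 78% | 80% |
| Three-group F test, means 0/0.5/1 | 78% | 80% |

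Each route needs an input that the article does not state, and neither reaches 80% for pain.

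**The case against.** **The mismatch is conservative.** For one pairwise contrast at 5%, 74 per arm is more than enough, recruitment was already under way, and no planned estimate or test changes. This stands, and it limits the weight of the point.

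**The figure of 65 presumes a pairwise t-test that the text never names.** This also stands. The supportable statement is that 74 cannot be reproduced from the stated inputs under a two-group comparison. It does not show that the unseen calculation was wrong. That the article is condensed does not answer the point, because the section prints inputs and a conclusion that do not agree.

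Three stronger readings are tempting, and the documents do not support them:

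- *The 80% belongs to no test or hypothesis.* It is attached to two named primary outcomes, each with its own difference and SD, and the article states a hypothesis and a model. What is missing is narrower: the link to a test, an alpha and a contrast.
- *The authors inflated for loss by multiplying by 1.15.* Some routes to 74 do this, but alpha 0.025 with SD 1.8 reaches 74.1 by the proper division by 0.85. How the number was obtained cannot be inferred.
- *Power for PTA to beat both other arms on both outcomes is only about 65%.* With 63 evaluable per arm, simulation gives roughly 64–69% (assumed correlation between outcomes 0.3–0.7), but only if UT is no better than Control. The Discussion expects UT to beat Control. If UT is 0.5 or 1 point better than Control and PTA 1 point better than UT, the figure is about 76–80%. The article also does not fix success on all four comparisons as the criterion.

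**Conclusion.** The point holds in a limited form. The stated inputs lead to 65 (pain) or 62 (PSFS) per arm under a two-sided two-group t-test, about 195 in total, against the stated 74 and 222. With 74 randomised and about 63 evaluable, power for a single 1-point contrast at 5% is about 86% for pain and 87% for PSFS. If an unstated alpha of 0.025 or an evenly spaced three-group F test lies behind the number, power is about 78% for pain and 80% for PSFS.

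The size and power in the paragraph therefore do not agree, but for a single contrast the trial is larger than required, not smaller.

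These figures assume two-sided testing, 15% loss in each arm, and SDs that apply to the quantity compared at 1 month. They are t-test or F-test approximations. The planned mixed model with group-by-time terms may differ somewhat, depending on whether 1.84 and 1.8 are SDs of scores or of change, which the section does not say.

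**What to change.** Keep 222 and restate the Sample size calculation paragraph so that size and power agree, in whichever form is true:

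- If the calculation was for a pairwise comparison: 74 per arm, about 63 evaluable after 15% loss, gives about 86% (pain) and 87% (PSFS) power to detect a 1-point difference between two arms at two-sided 0.05.
- If a split alpha or an omnibus test was used: state it, bring the Statistical analysis section into line with it, and give the power for each outcome (about 78% for pain and 80% for PSFS with 63 evaluable per arm).

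In either case, name the contrast or contrasts the figure applies to, and say whether the SDs are of scores or of change.

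The cost is one reworded paragraph, plus a sentence in the analysis section under the second form. Enrolment does not change.

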### Eligibility criteria

This study will be carried out with patients on the treatment waiting lists of two physical therapy teaching clinics in the city of Taubaté, São Paulo (approved by the Ethics Committee of Universidade Bandeirante Anhanguera n. 44720315.5.0000.5372). The patients will be invited personally by phone. This study will include patients who have had chronic, nonspecific low back pain for at least 3 months, aged between 18 and 80 years, and who are able to read and write in Portuguese and classified as low risk of having psychosocial factors involved [8] according to the Start Back Screening Tool (SBST-Brazil) questionnaire [30, 31]. Patients with a history of spinal surgery, serious spinal diseases, nerve root compromise, diseases associated with cognitive impairment confirmed by medical diagnosis, or pregnancy will be excluded.

### Procedures

Patients will be evaluated by a previously trained blinded assessor who will provide information on the procedures and criteria for study participation. The assessor will contact patients by phone to confirm their eligibility criteria and to fill out the SBST-Brazil questionnaire. In the case of acceptance of participation and compliance with the eligibility criteria, the patient will be forwarded to initial assessment.

The blinded assessor will collect data at the baseline utilizing a neutral communication style so as not to influence the therapeutic alliance involved in patient care. A coding system in follow-up assessments will be carried out to ensure blinding. After this initial procedure, eligible patients will be referred to the therapist responsible for the interventions. An independent researcher not involved in the recruitment and evaluation of patients will perform randomization using Microsoft Excel software random number generation. The secret allocation will be made using sequential, numbered, sealed opaque envelopes. Due to the nature of the study, it will not be possible to blind the therapist or patients. All researchers involved in the stages of this study will receive adequate training to carry out the activities. Patient recruitment will begin in September 2015 and the date of completion will be December 2016.

